**Methods:**

This study will proceed in two phases: an exploratory phase and a randomized controlled phase. In the exploratory phase, 22 participants with indications for dapagliflozin treatment will be evaluated before and after treatment initiation to ascertain the concrete effect size regarding oxalate and calcium-sparing effects. This data will inform the calculation of the study sample size (ranging from 17 to 104 participants) to include high-risk calcium oxalate kidney stone formers in a randomized controlled crossover study design. Treatment phases—one with dapagliflozin and one with placebo—will alternate with wash-out phases involving placebo. The primary outcome is the reduction of oxalate excretion in 24-hour urine samples compared to baseline values after 8 weeks of therapy. Secondary objectives include analysing effects on kidney function, the frequency of urolithiasis, and treatment tolerance. Additionally, in-depth metabolomics analyses will explore pathophysiological pathways during treatment. Investigators, patients, and research staff will be blinded to the randomization list. This study was initially registered under EudraCT (Nr:2022-000994-13) and has been transitioned to CTIS (Nr: 2024-519371-25-00) to comply with EU Regulation 536/2014, ensuring streamlined management and transparency.

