## 2. Materials and methods

### 2.1 Study aim and perspective

In summary, further research is needed to confirm the assumption that Dapagliflozin can reduce oxalate and/or calcium excretion and in further consequence reduce the risk and frequency of urolithiasis. Moreover, the real pathophysiological effects are unknown, which is why we also include preliminary and in-depth metabolomics analysis of blood and urine- to narrow down potential biochemical pathways.

As one of the most common diseases globally, urolithiasis has a prevalence of 1% to 20% combined with high comorbidity and treatment costs [1,2]; the relapse rate within the first 10 years after initial treatment is about 60% [3]. After the first episode of kidney stones lifestyle modification is recommended to every patient. Supplementation and pharmaceuticals are recommended to be reserved for recurrent episodes. High-risk patients need preventive therapy adjusted to their metabolic abnormalities [18–21,61].

The evidence for current stone-preventing therapies based upon the determining stone composition or on biochemistry measures is low. Furthermore, especially in high-risk patients, the outcome of the above-mentioned therapies varies widely and has a significant failure rate [21,62]. Recent studies focusing on urolithiasis event-rates however showed a reduction of the frequency [68, 69]. In the case that dapagliflozin decreases the incidence of urolithiasis regardless of underlying comorbid disease a serious alternative to repetitive surgical treatment can be offered to affected patients. Especially hyperoxaluric patients will benefit from the new case application of dapagliflozin concerning reduced urolithiasis risk.

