#### 2.2.2 Randomized controlled trial.

The second part, the main trial will also be a randomized cross-over single-center study in patients with a high risk of urolithiasis reoccurrence to show if dapagliflozin can modify the urine composition in hyperoxaluric patients with a high stone-forming risk. After a recalculation of the sample size based on the findings of the exploratory phase screenings of potential participants will run to gain the population needed for this trial section.

We hope to demonstrate that dapagliflozin is a new therapy option for high-risk stone formers with no known secondary causes. Participants eligible for the main trial must meet two key criteria: first, they must be selected from a group of patients with similar clinical profiles, specifically those classified as high-risk stone formers who have experienced a significantly increased frequency or severity of urolithiasis events in recent years. Second, they must not have any identifiable secondary causes for these events, such as known metabolic disorders, anatomical abnormalities, or medications known to predispose to stone formation (see 2.4 Trial participants).

After the end of the main trial, the participants of the main trial will be offered to be included in a follow-up trial. The participants will continue to get a daily oral dosage of 10mg dapagliflozin for a period of up to two years. By that, we would like to demonstrate the effect of dapagliflozin on the urolithiasis event rate in humans in the first prospective trial even if short-term or metabolomic data of the first two study phases will gain no new information about the pathophysiology and the pharmacologic pathways behind this disease.

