### 2.5 Hypothesis and Endpoints

#### 2.5.1 Null hypothesis of the main trial.

Dapagliflozin therapy is not associated with a reduction of oxalate excretion in 24-hour urine by at least 25% compared to the baseline value in hyperoxaluric patients with a high risk of urolithiasis reoccurrence.

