#### 2.5.2 Alternative hypothesis of the main trial.

Dapagliflozin therapy is associated with a reduction of oxalate excretion in 24-hour urine by at least 25% compared to the baseline value in hyperoxaluric patients with a high risk of urolithiasis reoccurrence.

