#### WP1. Screening (Pre-study phase, 4 Months).

**Objective:** WP1 includes a prospective analysis of all patients of the Division of Cardiology of the General Hospital of Vienna with a diagnosed cardiomyopathy, diabetes mellitus II and no established SGLT-2 inhibitor therapy. Furthermore, also patients of the Department of Urology of the General Hospital of Vienna with at least one event of urolithiasis and a high risk of reoccurrence will be screened in preparation for the main trial. Baseline data as mentioned earlier of all study participants of the exploratory phase are collected **Methods:** 22 potential study participants fulfilling defined exclusion and inclusion criteria and willing to participate in the exploratory phase will be recruited. Pre-screening of potential participants of the main trial.

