#### WP3: Recalculation and randomization.

**Objective** After analysing the effect size of dapagliflozin on the oxalate excretion from the date of the exploratory phase the needed number of participants for the main trial will be calculated. The WP1 already screened patients that are willing to participate will be randomized. **Methods:** effect and group size calculation as well as randomization of the patients of the main trial

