#### WP4. Wash-out phase I (week 7–12).

**Objective** Baseline data as mentioned earlier of all study participants are collected. **Methods:** Blood- and 24h-urine screenings in week 6 (respectively week 12 overall) to obtain baseline data of all subjects; daily oral placebo administration in preparation for treatment phase I.

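### The main-trial question and both hypotheses name hyperoxaluric patients, but the printed criteria select high-risk calcium-oxalate stone formers without any urinary oxalate criterion

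*Protocol article*

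**What the plan says.** Three places that set the confirmatory question name hyperoxaluric patients:

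- Section 2.2.2 gives the purpose of the main trial as "to show if dapagliflozin can modify the urine composition in hyperoxaluric patients with a high stone-forming risk".
- Section 2.5.1 states the null hypothesis "in hyperoxaluric patients with a high risk of urolithiasis reoccurrence".
- Section 2.5.2 states the alternative, that dapagliflozin "is associated with a reduction of oxalate excretion in 24-hour urine by at least 25% compared to the baseline value in hyperoxaluric patients".

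The places that say who is enrolled describe something else:

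- Section 2.4.3 requires calcium-oxalate stone formers at high risk of recurrence. High risk means at least two symptomatic or surgically treated stones in 10 years, and/or a single stone with a family history, early onset, metabolic syndrome or obesity.
- Section 2.4.4 mentions oxalate only once, as an exclusion (primary hyperoxaluria).
- The eligibility narrative in 2.2.2 asks for high-risk stone formers without identifiable secondary causes.
- WP1 considers urology patients "with at least one event of urolithiasis and a high risk of reoccurrence will be screened in preparation for the main trial".
- The abstract plans "to include high-risk calcium oxalate kidney stone formers in a randomized controlled crossover study design".

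The 24-hour urine in wash-out phase I is described in WP4 as "Blood- and 24h-urine screenings in week 6 (respectively week 12 overall) to obtain baseline data of all subjects". That is a measurement on people already in the trial, not a condition of entry.

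**The concern.** A confirmatory hypothesis names the population to which its conclusion applies. Here the hypotheses name patients with raised urinary oxalate, while the enrolment rules never ask whether oxalate is raised. If the trial is positive and the hypotheses are read as written, the report would say that dapagliflozin lowers oxalate excretion in hyperoxaluric patients, a group the trial did not select.

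The mismatch matters more than usual because the primary endpoint is oxalate excretion itself. Baseline oxalate status is one of the first things a clinician would ask about when deciding whom the result concerns. Section 2.1 already points that way: "Especially hyperoxaluric patients will benefit from the new case application of dapagliflozin concerning reduced urolithiasis risk". That sentence treats hyperoxaluric patients as a subgroup of the wider target population, which is hard to square with hypotheses that treat them as the whole of it.

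**Working it through.** **Step 1. Look for an oxalate entry criterion.** This is a comparison of texts; no figure in the plan needs reproducing.

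| Place | Population or rule | Oxalate level used for entry? |
|---|---|---|
| 2.2.2, purpose | hyperoxaluric, high stone-forming risk | named, not defined |
| 2.5.1 and 2.5.2 | hyperoxaluric, high recurrence risk | named, not defined |
| Abstract, Methods | high-risk calcium-oxalate stone formers | no |
| 2.2.2, eligibility narrative | high-risk stone formers, no secondary cause | no |
| 2.4.3 | calcium-oxalate stone formers by stone history or risk factors | no |
| 2.4.4 | excludes primary hyperoxaluria, bowel disease and others | no threshold; exclusions only |
| WP1 | at least one stone event and high recurrence risk | no |
| WP4 | week-12 urine as baseline data for all subjects | no |

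The criteria lists are detailed: they print cut-offs for BMI, eGFR, potassium and sodium. They contain no cut-off for urinary oxalate, and the article gives no definition of hyperoxaluria.

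**Step 2. Ask whether the two descriptions could mean the same group.** Section 1.2.1 cites a cohort of 1,270 patients with recurrent stones. The frequencies were hypercalciuria 61%, hypocitraturia 28%, urine volume below 1.0 L/day 15% and hyperoxaluria 8%. By the document's own background, forming recurrent stones does not imply hyperoxaluria.

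**Step 3. Illustrate the size.** Inputs: the main-trial range of 17 to 104 participants (abstract), and a share p of hyperoxaluric patients among those enrolled. The documents do not give p for this trial. The 8% is the only related figure; the other values are assumptions chosen to show a range. Expected number = N × p.

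| Assumed p | N = 17 | N = 104 |
|---|---|---|
| 8% (cited cohort) | 17 × 0.08 = 1.4 | 104 × 0.08 = 8.3 |
| 20% | 3.4 | 20.8 |
| 30% | 5.1 | 31.2 |
| 50% | 8.5 | 52.0 |

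The range 17 to 104 includes the 20% dropout allowance. For Table 1's group sizes before dropout, 14 to 86, the 8% row becomes 14 × 0.08 = 1.1 to 86 × 0.08 = 6.9.

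At every share shown, at least half of those enrolled would lie outside the population named in the hypotheses. The conclusion in step 1 does not depend on this table.

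**The case against.** The strongest reply is that this is loose vocabulary. The abstract, the inclusion list and WP1 agree that high-risk stone formers are meant, and section 1.4 uses hyperoxaluric as a label for a type of stone. On that view the operative population is clear and only three phrases depart from it. Much of this stands, and it is why rewording is the right remedy. It does not remove the point, because those three phrases are the trial question and both confirmatory hypotheses, which govern what a positive result may claim.

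A second reply is that the full protocol may hold an oxalate threshold. An article may condense detail, but this one prints specific inclusion and exclusion lists, and the population they define differs from the one in its hypotheses.

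A third reply concerns the 8%. It comes from recurrent stone formers in general and was not adjusted for underlying disease. Restricting to calcium-oxalate formers could raise the share; excluding primary hyperoxaluria and bowel disease could lower it. This objection stands in full. The 8% shows that the two groups differ, and it does not predict this trial's case mix.

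A reader might also infer that no urine oxalate result can be available before randomisation. The documents do not settle that. WP3 says that "The WP1 already screened patients that are willing to participate will be randomized", but 2.6.2 mentions randomisation within its description of wash-out phase I. The exclusion for hyperuricosuria implies some urine chemistry before entry, and the schedule figures are not shown. What can be said is narrower: no printed criterion makes entry depend on oxalate.

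**Conclusion.** The point holds as an inconsistency in the current text. As written, a positive result supports a statement about high-risk calcium-oxalate stone formers, and the hypotheses would attach it to hyperoxaluric patients. How far the two populations differ in practice is unknown; at 8% the trial would hold about 1 to 8 hyperoxaluric patients, and more if the true share is higher. The textual finding needs no assumption beyond the printed criteria being the ones applied.

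Two stronger readings should be resisted. A reader might infer that the dapagliflozin–placebo comparison is invalid. The mismatch does not show that: the comparison is randomised and made within the patients enrolled, whatever they are called. A reader might also infer a definite gain or loss of power. Power depends on the achievable reduction and its variability, and the documents do not show how either relates to baseline oxalate, so no statement on power is warranted in either direction.

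The correction should be made before results are known, because it decides which population the confirmatory conclusion may name.

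**What to change.** In 2.2.2, 2.5.1 and 2.5.2, replace hyperoxaluric patients with high-risk calcium oxalate stone formers as defined in 2.4.3, in line with the abstract. The sentence in 2.1 about hyperoxaluric patients benefiting especially can stay as an expectation about a subgroup.

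The cost is three wording changes, with no change to eligibility, endpoint, visit schedule or sample size method. The small downside is that the claim is no longer specific to hyperoxaluria.

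Adding an oxalate threshold to 2.4.3 would also remove the contradiction, but it is a different and more expensive trial. The number of otherwise eligible patients to screen per patient randomised is 1/p: 12.5 at 8%, 5 at an assumed 20%, 2 at an assumed 50%. At 8% that means about 213 screened for 17 randomised (17/0.08) or 1,300 for 104 (104/0.08). It makes sense only if hyperoxaluric patients are truly the intended target, which the rest of the document does not suggest.

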#### 2.5.2 Alternative hypothesis of the main trial.

Dapagliflozin therapy is associated with a reduction of oxalate excretion in 24-hour urine by at least 25% compared to the baseline value in hyperoxaluric patients with a high risk of urolithiasis reoccurrence.

#### 2.5.3 Primary endpoint of the main trial.

As the primary endpoint, we chose *the reduction of the urine oxalate excretion after 8 weeks of dapagliflozin therapy* compared to the baseline value that was collected in the washout phase before the treatment period.

As a secondary objective, we chose to compare the oxalate and calcium-sparing effects such as the kidney function, the frequency of urolithiasis events within the study period, and the tolerance to each treatment. The rationale behind this is a combination of two findings: 1) the reduced urolithiasis event rate under SGLT-2 inhibitor therapy in former trials [68, 69] and 2) the reduced oxalate excretion in a rat model about the effect of SGLT-2 inhibitors on urolithiasis [69]. Further, AstraZeneca holds a patent for the use of SGLT-2 inhibitors to prevent and treat kidney stones [81].

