### 2.3 Sample size calculation

#### 2.3.1 Sample size calculation of the exploratory phase.

As mentioned above, no data exists about the effect of dapagliflozin on the oxalate and calcium 24-hour urine excretion. Given the observed decrease in urolithiasis event rates in previous studies [68,69] and findings from a rat model investigating the impact of SGLT-2 inhibitors on urolithiasis [69] we anticipate a 10%-50% reduction in 24-hour urinary excretion of oxalate and calcium compared to placebo. This expectation is supported by evidence suggesting that a 10% decrease in urinary excretion of calcium and oxalate is linked to a significant 8% reduction in the risk of recurrence [76]. We, therefore, expect a) the effect size of dapagliflozin to be a reduction of urinary excretion of lithogenic molecules between 15% and 25% reduction and b) subsequently to have a clinically relevant potential to lower the risk of urolithiasis reoccurrence.

The sample size calculation is based on our primary outcomes of the intraindividual comparisons. The sample size calculation based on a paired t-test was performed using G*Power Version 3.1.9.4. The significance level of two-sided testing was set to 0.025 to acknowledge the two primary endpoints [80]. We set the power to 90% and the alpha error to 5%. Due to no comparable data, we assume a standard deviation of 20% and a correlation between the intraindividual comparisons of 0.1. Based on the sample size models in Table 1. (assumed effect size of 25%, correlation between the groups of 0.1) we proclaim a group size of 18 participants plus an expected dropout rate of 4 so a total of 22 participants is reasonable.

**Table 1 pone.0322034.t001:** potential group size calculations based on earlier findings.

Mean difference	Mean ± SD group 1	Mean ± SD group 2	Group size	Group size + 20% dropout
10%	1.0 ± 0.2	1.1 ± 0.22	86	104
15%	1.0 ± 0.2	1.15 ± 0.23	42	51
20%	1.0 ± 0.2	1.2 ± 0.24	26	32
25%	1.0 ± 0.2	1.25 ± 0.25	18	22
30%	1.0 ± 0.2	1.3 ± 0.26	14	17

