## 3. Statistics

### 3.1 Statistical analysis

We plan to perform statistical analysis conforming to the standard methodology. Categorized data will be presented as absolute count and relative frequencies. Continuous data will be reported as mean and standard deviation in case of normal distribution and as median and inter-quartile range (IQR) in case of a non-normal distribution. Two-sided tests are considered to be significant with a p-value <0.05.

Analyses of continuous variables will be performed using parametric and non-parametric tests (paired t-test/ Mann-Whitney-U-test). The primary endpoint is confirmatory and is the reduction of oxalate in the Verum vs. Placebophase, i.e., Dapaglifozine vs. placebo which will be compared with a two sided-t-test. Intergroup comparisons (Dapaglifozine vs placebo) will be performed by an ANOVA for a crossover design on the group of patients who went through all trial phases and corrected with Bonferroni post-hoc Tests for multiple testing. Frequencies of urolithiasis will be tested with the x²-test, a in comparison of both treatments by the McNemar-Test. Correlations between variables will be performed using Pearson or Spearman coefficients.

Findings will be corrected for multiple testing using the Tukey method if the statistical analysis is performed with a one-way ANOVA or with the Shaffer correction if the statistical analysis is performed with a Kruskal-Wallis test. All other statistical tests will be corrected using the Bonferroni-Holm method.

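### The confirmatory primary is defined against the patient's own baseline in some sections and against the placebo phase in others; the baseline version leaves the randomised control out of the main claim

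*Protocol article*

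**What the plan says.** Two comparators are given for the same confirmatory endpoint.

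**Own baseline.**
- Abstract, Methods: "The primary outcome is the reduction of oxalate excretion in 24-hour urine samples compared to baseline values after 8 weeks of therapy".
- Section 2.5.3: the reduction after 8 weeks of dapagliflozin "compared to the baseline value that was collected in the washout phase before the treatment period".
- Section 2.5.1 (null): "Dapagliflozin therapy is not associated with a reduction of oxalate excretion in 24-hour urine by at least 25% compared to the baseline value". Section 2.5.2 states the alternative with the same comparator and threshold.
- Section 2.3.2 (main-trial sample size) also refers the effect to the baseline value, and speaks of oxalate concentration where the other sections speak of excretion.
- WP9 restates a 25% reduction under dapagliflozin after 8 weeks and does not mention placebo.

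**Placebo phase.**
- Sections 2.6 and 3.1: "The primary endpoint is confirmatory and is the reduction of oxalate in the Verum vs. Placebophase", that is, dapagliflozin against "placebo which will be compared with a two sided-t-test".
- Section 3.1 then also names a crossover ANOVA for dapagliflozin versus placebo.
- Section 2.6.2 describes a within-patient comparison of dapagliflozin with placebo, and 2.3.1 states the anticipated effect relative to placebo.

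**Sample size.** Section 2.3.1: "The sample size calculation is based on our primary outcomes of the intraindividual comparisons", using a paired t-test with SD 20% and a correlation of 0.1.

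Nothing in the article reconciles the two comparators. Nor does it say whether the reduction compared between phases is a change from each period's baseline or a difference between on-treatment values.

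**The concern.** These are different quantities. The baseline version takes one urine before and one after dapagliflozin. The placebo period does not enter it, so a blinded randomised crossover becomes a before-after study for its main claim, and any change over time after the baseline (season, dietary behaviour, regression to the mean) counts as drug effect. The placebo version is controlled, but it has two forms with different variances, and the sample-size model fits only one of them.

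Two definitions of one confirmatory endpoint also allow either result to be presented as prespecified. The main-trial sample size is still to be recalculated, and it cannot be computed properly until the contrast is fixed.

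**Working it through.** **1. Reproducing Table 1.** Inputs from 2.3.1: SD 20% of each mean, r = 0.1, power 90%, paired t-test (non-central t).
- SD of the difference = √(s₁² + s₂² − 2·r·s₁·s₂).
- 25% row: √(0.20² + 0.25² − 2·0.1·0.20·0.25) = √0.0925 = 0.304, so d = 0.25/0.304 = 0.822.
- At two-sided 0.05 the five rows give 86, 42, 26, 18 and 14, exactly as printed. At the stated 0.025 they give 102, 49, 30, 21 and 17.
- Power at n = 18 in the 25% row is 0.907 at 0.05 and 0.837 at 0.025.

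The planned variance is therefore that of one difference between two urines.

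**2. Placebo version read as a difference of changes.** The contrast is (T₁ − B₁) − (T₂ − B₂), which uses four urines. With equal SDs and equal correlations between periods, the between-period terms cancel and the variance is 4σ²(1 − r_w), where r_w is the correlation between baseline and on-treatment urine in one period. The planned variance is 2σ²(1 − 0.1) = 1.8σ².

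| r_w | Variance ratio to plan | Power at n = 18, two-sided 0.05 | Power at n = 18, two-sided 0.025 |
|---|---|---|---|
| 0.1 (the plan's value) | 3.6/1.8 = 2.00 | 0.643 | 0.517 |
| 0.3 | 2.8/1.8 = 1.56 | 0.750 | 0.636 |
| 0.5 | 2.0/1.8 = 1.11 | 0.876 | 0.793 |
| 0.55 | 1.8/1.8 = 1.00 | 0.907 | 0.837 |

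At r_w = 0.1, d falls to 0.822/√2 = 0.581, and 90% power needs 34 pairs instead of 18 (40 instead of 21 at 0.025). The ratio comes from the equal-SD formula and is applied to the Table 1 variance of 0.0925. Giving the baseline and the placebo-period urines the larger SD of 0.25 and the dapagliflozin urine 0.20 makes the ratio 2.22 and the number of pairs 37 (44 at 0.025). A direct comparison of on-treatment values between periods keeps the planned variance if their correlation is 0.1.

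**3. Baseline version with no drug effect (illustration only).** The drift is an assumption. With SD 20% and r = 0.1, the SD of the difference is √(0.04 × 1.8) = 0.268. Probability of a significant result when testing against zero:

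| Drift | n = 18, 0.05 | n = 18, 0.025 | n = 42, 0.05 |
|---|---|---|---|
| 5% | 0.12 | 0.07 | 0.22 |
| 10% | 0.32 | 0.22 | 0.65 |

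Against the 25% threshold that 2.5.1 states, the same drifts lead to a declared success with probability below 0.0001 at either n.

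**4. Timing.** The abstract, 2.5.3 and WP9 refer to 8 weeks. Section 2.6.2 and WP5–WP8 list urine at treatment week 4 (overall weeks 16 and 30) and in washout week 1 (weeks 21 and 35). No collection is listed in treatment week 8.

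**The case against.** The strongest reply is that the sections fit together: 2.5.3 defines the variable (change from the preceding washout value), and 2.6 and 3.1 define the contrast (that change, dapagliflozin versus placebo). Both of those sections attach the confirmatory label and the t-test to the placebo comparison, and no section assigns a test to the before-after comparison. This is a possible reading, and a reader who infers that an uncontrolled analysis is definitely planned goes further than the text. But the formal hypotheses, the section headed as the primary endpoint and WP9 all describe a reduction without placebo, so the statistics section does not settle the matter. The compatible reading is also the one under which Table 1's variance does not apply.

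Other parts of the reply stand:
- The drift figures test against zero, whereas 2.5.1 sets a 25% threshold. They are not the trial's error rate.
- Dietary advice applies throughout, and baseline is taken in week 6 of a placebo washout, so much of any early dietary response would already be in the baseline. Later trends remain possible.
- The n = 18 row was chosen for the single-arm exploratory phase. The main-trial number is to be recalculated, so the power loss applies only if those inputs are carried over.
- The correlation of 0.1 was assumed for want of data.
- The log scale and the choice of a mixed model over the named crossover ANOVA are matters of preference.

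**Conclusion.** The contradiction is real, sits in the current text and concerns the confirmatory endpoint. It must be resolved before the sample size is recalculated. Followed as written, the baseline version leaves the placebo period and the randomisation out of the main claim. That conclusion depends on none of the figures above.

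The sizes are conditional. The fall in power from 91% to about 64% (84% to 52% at 0.025) needs three things: the difference-of-changes reading, a baseline to on-treatment correlation of 0.1, and reuse of the 25% row with n = 18. A reader might infer that the main trial will have half its planned information. The article does not support that, because the main-trial number is not fixed and the loss has disappeared at a correlation of 0.55. A reader might also infer a false-positive rate of 12% to 32%; that requires an assumed drift and a zero null that 2.5.1 does not state.

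**What to change.** State one primary: the within-patient difference, dapagliflozin versus placebo, in 24-hour oxalate excretion at one named collection that is already scheduled. Reconcile the 8-week wording with a schedule that lists urine at treatment week 4 and washout week 1.

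Analyse that contrast with the crossover model (treatment, period, sequence, patient) and drop the separate t-test as a second primary analysis. Enter the period baselines as covariates rather than subtracting them, and report change from baseline descriptively.

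Align the abstract, 2.3.2 (including concentration to excretion), 2.5.1–2.5.3, 2.6, 3.1 and WP9, and base the main-trial sample-size recalculation on the variance of the chosen contrast.

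The cost is protocol and analysis-plan wording plus one recalculation that is planned anyway. Both period baselines are already scheduled. If a treatment week 8 value is wanted, the article does not show that it would be collected, and the cost would then include a change to the schedule.
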